## Abstract

**Introduction:**

Pulmonary rehabilitation (PR) is a programme of individually prescribed physical exercise, education and self-management activities. PR is recommended in international guidelines for managing chronic obstructive pulmonary disease (COPD) and other chronic respiratory diseases. PR is still under-recognised in tuberculosis (TB) guidelines and PR is not available in many low and middle-income countries and for people with post-TB lung disease (PTBLD). The main aims of the study are to adapt and define a culturally appropriate PR programme in Kyrgyzstan for people living with PTBLD and to test, in a fully powered randomised controlled trial (RCT), the effectiveness of PR in improving exercise capacity for people living with PTBLD.

**Methods and analysis:**

The study will be divided into three stages: *stage 1:* focus group discussions with patients living with PTBLD and interviews with PR referrers will be conducted to explore initial perceptions and inform the cultural adaptation, structure and content of PR. *Stage 2a:* a single-blind RCT evaluating the effectiveness of a culturally adapted 6-week PR programme on maximal exercise capacity, assessed by the incremental shuttle walking test, before and after PR. Participants will be additionally followed-up 12 weeks postbaseline. Additional outcomes will include health-related quality of life, respiratory symptoms, psychological well-being and physical function. *Stage 2b:* participants’ experience of PR will be collected through interviews and using a log book and a patient evaluation form. Staff delivering PR will be interviewed to explore their experience of delivering the intervention and refining the delivery for future implementation.

**Ethics and dissemination:**

The study was approved 22/07/2019 by Ethics Committee National Center for Cardiology and Internal Medicine (reference number 17) and by University of Leicester ethics committee (reference number 22293). Study results will be disseminated through appropriate peer-reviewed journals, national and international respiratory/physiotherapy conferences, social media, and through patient and public involvement events in Kyrgyzstan and in the UK.

**Trial registration number:**

ISRCTN11122503.

Strengths and limitations of this studyThis project will inform an appropriate pulmonary rehabilitation programme for people living with post-tuberculosis lung disease (PTBLD) in Kyrgyzstan. This study is the first fully powered randomised controlled trial (RCT) of a culturally appropriate pulmonary rehabilitation programme for adults with PTBLD in Central Asia.This is a single-centre fully powered RCT; while findings will be important for assessing impact of pulmonary rehabilitation in Kyrgyzstan, Central Asia and low and middle-income countries (LMIC) more broadly, findings may not be generalisable to other parts of the world.Taking a mixed-method approach, this study will provide a rich insight into the experiences of pulmonary rehabilitation for people living with PTBLD.Using a common set of outcome measures specifically designed for pulmonary rehabilitation in LMIC will allow for direct comparisons of outcomes between sites across the world.

## Introduction

### Background and rationale

Tuberculosis (TB) is an infectious disease and a major cause of death worldwide.^1^ It typically affects the lungs (pulmonary TB) and approximately a quarter of people globally are at risk of developing TB.^1^ Every year, approximately 10 million people worldwide develop TB,^2^ of which 500 000 are multidrug-resistant cases.^3^ Pulmonary TB remains an important cause of chronic respiratory impairment in low and middle-income countries (LMIC) and globally. Kyrgyzstan is classified as lower middle income country, is situated in Central Asia and has a higher respiratory mortality compared with Europe, with a TB incidence of 100:100 000.^4^

The presence of long-term respiratory sequelae following pulmonary TB treatment is well established.^5 6^ The persistence of abnormal airway physiology,^7^ specifically fixed airways obstruction after treatment, has been documented in large population-based cross-sectional studies. The consequence of suffering from pulmonary TB is termed post-TB lung disease (PTBLD). PTBLD negatively impacts people’s quality of life, with exercise intolerance, respiratory symptoms and abnormal lung function.^8 9^ PTBLD also poses a significant economic burden to individuals and societies, not only attributable to direct costs of drugs and hospital stay but also indirect costs such as missed workdays or lower productivity. The burden of PTBLD alongside the economic conditions in LMIC such as Kyrgyzstan aggravates the situation of patients, leading to disability and early mortality.^10^

Pulmonary rehabilitation (PR) is a programme of individually prescribed physical exercise, education and self-management activities. PR is recommended in international guidelines for managing chronic obstructive pulmonary disease (COPD) and other lung diseases^11^ but is still under-recognised in TB guidelines and in LMIC.^12^ With the established benefits of PR for people living with chronic respiratory diseases, many high-income countries have integrated PR services within routine healthcare services. Delivery of PR is encouraged in LMIC where there is profound need,^13^ where there is emerging evidence that it is feasible to deliver PR in low-resource settings,^14 15^ including for people living with PTBLD^16^ for whom post-treatment support for health and well-being is needed.^17^ Indeed, PR is typically delivered by a multidisciplinary team, which has been advocated for people living with PTBLD in order to account for psychosocial and economical challenges.^18 19^ Western models of PR may not be optimal in LMIC and there is a need to implement PR interventions tailored to the local culture, traditions, geography, population and healthcare systems. To date, despite the potential to improve patient outcomes in PTBLD, there has been no formal fully powered trial of PR for people living with PTBLD in LMIC. It is important for PR to be appealing to patients and to ensure that it is delivered in a manner sensitive to local contexts. Accordingly, the aim of this study is to adapt a conventional model of PR to Kyrgyzstan and PTBLD contexts and test its effectiveness in a fully powered randomised controlled trial (RCT).

The trial is comprised of: stage 1: adaptations to PR informed by patients living with PTBLD and healthcare professionals (HCPs) who would refer to PR; stage 2a: fully powered RCT; and stage 2b: qualitative evaluation of PR. The objectives of this study are to:

Explore the views of people living with PTBLD and HCPs (referrers and deliverers) involved in the care of patients living with PTBLD to inform the adaptations needed for a PR programme suitable for people living with PTBLD in Kyrgyzstan.Conduct a single-blind fully powered RCT to assess the effectiveness of adapted 6-week PR on maximal exercise capacity (assessed by the incremental shuttle walking test (ISWT)).Evaluate a range of secondary outcome measures including health-related quality of life, respiratory symptoms, functional status and psychological well-being following PR.Assess any further changes in all outcome measurements 12 weeks postbaseline.Assess the acceptability of PR of participants and the staff delivering PR to inform further improvements to the service.

## Methods and analysis

### Trial design

The trial will be conducted, analysed and reported according to the Standard Protocol Items: Recommendations for Interventional Trials statement and the trial has been prospectively registered.

#### Stage 1

Focus groups with adults living with PTBLD and interviews with staff who would be involved in referring patients to PR will be conducted to explore initial perceptions of PR and to inform the cultural adaptation of PR, for their insight, any minor modifications and any additional needs, so that it is suitable for this group and for understand their views on any specific topics for the health education component, or any types of exercises that are suitable for enjoyment and adherence for this population.

#### Stage 2A

After the PR programme has been adapted based on the qualitative work at stage 1, an RCT evaluating the effectiveness of PR in adults with PTBLD. Adults living with PTBLD will be randomly allocated into one of two groups: group A (assigned PR programme) or group B (usual care on PR waiting list).

#### Stage 2B

On completion of PR, patient focus groups and interviews with staff who were involved in the delivery of PR will be conducted. Participants in the PR group will be asked to log their experience as they progress through the programme by completing a log book accessible before, during and after sessions as well as a dedicated patient evaluation form to be completed after their last class.

### Study setting

The study will be conducted at the National Center for Cardiology and Internal Medicine (NCCIM), Bishkek, Kyrgyzstan. Interviews will be conducted in quiet and familiar settings, for example, a HCP’s office. Spacious and quiet rooms will be used for focus groups. For the PR programme, a specially allocated room with the necessary equipment and air conditioner will be used. For all stages of the project, appropriate precautions will be taken in line with local COVID-19 guidance.

### Participants

For stage 1, eligible patients will be: aged ≥18 years; confirmed diagnosis of TB-negative patients with PTBLD using a Ziehl-Nielsen stain or GeneExpert method and completed TB treatment. Eligible HCPs will be directly involved in the long-term care of patients with PTBLD.

For stage 2a, the inclusion criteria for patients will be: aged ≥18 years; confirmed diagnosis of a TB-negative patients with PTBLD using a Ziehl-Nielsen stain or GeneExpert method; completed TB treatment; Medical Research Council (MRC) dyspnoea score grade 2 or higher. Exclusion criteria for patients will be: comorbidities such as severe or unstable cardiovascular, other internal diseases and locomotor difficulties that preclude exercise; malignant disease such as lung cancer; evidence of active TB on chest X-ray or sputum tests within 1 month of assessment; unable or unwilling to provide informed consent.

For stage 2b, all patients consented and randomised to receive PR and all staff involved in the delivery of PR to patients as part of the trial will be eligible.

### Procedure

After receiving a research fact sheet, patients eligible for the study will be asked if they would like to participate after they have had the opportunity to ask questions. If they wish to take part, they will be asked to provide written informed consent (Appendix A). Reasons for declining the study will be taken as field notes. If they wish to participate, they will be asked to provide written informed consent. Reasons for declining to participate will be reflected in the field notes. The staff of the family medicine centres, doctors of the City Tuberculosis Hospital, the City Tuberculosis Dispensary, the National Hospital, District Hospitals and the National Centre of Cardiology and Internal Medicine will screen patients for eligibility and refer interested patients to the PR study team. Interested patients will be screened by the study team to confirm interest in participation and to schedule the baseline visit. After providing written informed consent, participants will undergo a baseline assessment at the NCCIM by a specially trained team of researchers and residents. After the baseline measures are complete, participants will be randomised into one of two groups: PR or usual care control. At 6-week postbaseline and 12-week postbaseline, patients will undergo follow-up assessments. If participants are not able to attend follow-up assessments in person, questionnaires only will be completed via telephone appointment. Experiences of the patients living with PTBLD and PR deliverers will be explored in interviews and focus groups. Participants who drop out of the trial will be asked to take part in an interview and information provided freely by the participants will be collected as field notes. All outcome measures will be performed at 6 and 12 weeks by dedicated staff who are blinded to group allocations. Control participants will be offered PR at the end of the study (see figure 1).

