### Intervention

The PTBLD PR programme will be held two times weekly for a period of 6 weeks. Each session will last approximately 2 hours, consisting of exercise and health education (online supplemental table 1). The PR programme recruitment will be rolling rather than fixed groups, with a maximum capacity of five patients per session (due to pandemic) and supervised by a nurse, doctor, researcher or physiotherapist. The equipment used will be simple and based on local availability. It will be based on the core elements of an evidence-based rehabilitation, including exercises and health education, but we will be adapting the detail and delivery based on the qualitative work in Stage 1.

10.1136/bmjopen-2021-048664.supp1Supplementary data

Core components of PR exercise are upper and lower body resistance training and aerobic training will be informed by international guidelines.^11 20^ The strength exercises will include (at least) bicep curls, pull-ups, sit-to-stands and step ups. Patients will be asked to do one session of strength training and to walk every day at home in addition to structured classes. Minimal equipment will be used where possible, such as bottles filled with water, to achieve the desired weight in kilograms and to offer insight into how participants can exercise effectively at home during and after finishing PR. Aerobic exercise will include walking and static cycling. Walking will be individually prescribed at a speed equivalent to 85% maximal oxygen capacity (VO_2_) peak derived from the ISWT.^21 22^ Walking will be monitored and target duration increased by the instructor as the programme progresses. The content delivered within the education sessions will be based on existing materials, with refinement from stage 1 of this trial and will be delivered by an interdisciplinary team.

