#### Stage 2a

Assuming a statistical significance level of 5% and a statistical power of 80%, in order to detect a 35 m difference in ISWT measured at baseline and after completion of PR,^23^ a total of 114 participants are required (PR: 57 participants or waiting list control: 57 participants). This power calculation was performed using a paired t test and assumes the ISWT follows an approximately normal distribution. Data from a feasibility study in Uganda, assessing PR in a PTBLD population, have guided this calculation.^14^ Conservatively assuming up to 30% loss to follow-up at 6 weeks, this will require up to 114 participants to be recruited and randomised (1:1) to each arm. The estimated 70% ineligibility rate suggests approximately 543 patients with PTBLD will be screened for this trial.

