### Randomisation

Randomisation will occur through a web-based service Sealed Envelope and conducted in a designated room by a dedicated member of the research team. Participants will be randomised (1:1) to either PR or usual care. A dedicated member of the research team will inform the assessors of group allocations via telephone. Participants will be informed at the end of their baseline visit to arrange their first PR class.

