##### Physical activity

Physical activity will be assessed using an ActiGraph wGT3X-BT activity monitor (ActiGraph, Pensacola, Florida). Participants will be asked to place the device on their right anterior hip during waking hours for 1 week prior to attending PR (baseline) and for 1 week prior to their 6-week follow-up visit. Participants will be asked to remove the device for water-based activities and for sleep. Written instructions will be provided to the participants. Full methodology for the assessment of physical activity is provided in online supplemental table 2.

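### The primary ISWT visit is set at 6 weeks after baseline, the full length of the programme, so it is a post-PR assessment only if classes start within about 2–3 days of baseline

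*Protocol article*

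**What the plan says.** All references are to the protocol article.

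- **Visit timing (Procedure).** "At 6-week postbaseline and 12-week postbaseline, patients will undergo follow-up assessments". The abstract and the Outcomes section also count the later visit from baseline.
- **Programme length (Intervention).** "The PTBLD PR programme will be held two times weekly for a period of 6 weeks", which makes 12 sessions. Entry is "rolling rather than fixed groups, with a maximum capacity of five patients per session".
- **Order of events (Procedure, Randomisation).** "After the baseline measures are complete, participants will be randomised into one of two groups: PR or usual care control". Then: "Participants will be informed at the end of their baseline visit to arrange their first PR class".
- **Activity monitor (Physical activity).** Worn "for 1 week prior to attending PR (baseline) and for 1 week prior to their 6-week follow-up visit". Table 1 lists this monitoring in the face-to-face baseline column.
- **What the first follow-up is meant to be.** The sample size for Stage 2a is built on a "35 m difference in ISWT measured at baseline and after completion of PR". The abstract describes the ISWT as done before and after PR, and the Blinding section calls the visit post-PR.

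The article does not give the interval from baseline to the first class, and does not tie the 6-week visit to the last session.

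**The concern.** The primary endpoint is timed in two ways. One clock starts at baseline and runs for 6 weeks. The other ends when the programme ends. Because the programme also takes 6 weeks and starts after baseline, the two agree only when PR begins almost at once. The steps between baseline and the first class (randomisation, arranging a class, finding a place in a capped session) make some delay likely for at least some participants.

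If the baseline clock is followed, anyone who starts later than a few days after baseline has the primary outcome measured before finishing the intervention, and the estimated effect would be expected to shrink towards zero. If the completion wording is followed, PR participants would be seen later than controls, who have no completion date, and the arms would be compared at different times since randomisation.

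**Working it through.** **Inputs.** Visit on day 42 after baseline (Procedure). Twelve sessions, two per week for six weeks (Intervention). Target difference 35 m, 57 per arm, 5% significance, 80% power (Sample size, Stage 2a). Assumptions: the two weekly sessions are 3 or 4 days apart, the test is two-sided, and the SD, which is not given, is back-solved.

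**Step 1: when the last session falls.** If the first session is on day d, the sixth week starts on day d + 35, so the last session is on day d + 38 (3-day gap) or d + 39 (4-day gap). It precedes day 42 only if d ≤ 3 or d ≤ 2 respectively.

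| First session | Last session | Sessions before day 42 |
|---|---|---|
| Day 0 | Day 38–39 | 12 |
| Day 2 | Day 40–41 | 12 |
| Day 3 | Day 41–42 | 12 or 11 |
| Day 5 | Day 43–44 | 11 |
| Day 7 | Day 45–46 | 10 (an eleventh falls on day 42 itself) |
| Day 14 | Day 52–53 | 8 (a ninth falls on day 42 itself) |

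The schedule therefore has about 3 days of slack.

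**Step 2: where the monitor week falls.** If the monitor is issued at the baseline visit and worn for the following 7 days before PR, then d ≥ 7, and 12 − 10 = 2 sessions are still to come when a day-42 visit is made. If the week lies before the visit, or inside a baseline period that closes at randomisation, it adds no lag. The Procedure section describes referral, screening, consent and baseline assessment with no earlier visit for issuing a monitor. That favours the first reading without settling it.

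**Step 3: the plan's own sample size.** Without an SD, 57 per arm cannot be reproduced forwards. Solved backwards at two-sided 5% and 80% power, it implies an SD of about 66.1 m for a two-sample t test with 57 per arm, or an SD of change of about 92.7 m for the paired t test that the section names, with n = 57. The timing conflict depends on neither.

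**Step 4: illustrative dilution.** Assume the gain is proportional to sessions delivered before the visit. For the two-sample test, power is the upper tail of a noncentral t with 112 degrees of freedom and noncentrality (effect/SD) × √(57/2).

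- 12 of 12: 35 m; noncentrality (35/66.1) × 5.34 = 2.83; power 80%.
- 11 of 12: 35 × 11/12 = 32.1 m; power 73%.
- 10 of 12 (one-week lag): 35 × 10/12 = 29.2 m; noncentrality 2.36; power 65%.
- 8 of 12 (two-week lag): 35 × 8/12 = 23.3 m; noncentrality 1.88; power 46%.

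The paired test with its own back-solved SD gives the same powers to the nearest percentage point, so the choice of test does not drive the illustration.

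**The case against.** The strongest reply is that nothing in the article says PR starts a week after baseline. The monitor week is itself labelled baseline, Table 1 places it in the baseline column, and randomisation waits until baseline measures are complete. On that reading the week is over before randomisation, the 6 weeks run from its end, and a prompt first class lets all 12 sessions finish by day 38–41. This stands. A reader might infer that PR always starts at least a week after baseline and that the 6-week visit cannot follow completion; the documents support neither as fact.

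Nor does the primary objective demand completion: it names 6-week PR and says nothing about when the ISWT is taken. The completion wording is in the sample size, and similar wording is in the abstract and Blinding section.

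A reader might also take the cap of five per session as proof of long queues. It is not: the number of sessions run in parallel is not stated, and overall throughput does not give any individual's waiting time. Different assessment times by arm are likewise not planned, since the Procedure section gives both arms the same visits. They would arise only if staff acted on the completion wording.

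The power figures rest on a back-solved SD and on a linear gain, although participants are also asked to exercise at home. They are illustrations only.

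Finally, start-lag rules and visit windows may sit in the full protocol, the flow figure or the supplement. Their absence here is not the point. The article states two timings for its primary assessment, and they coincide only under a condition that it does not set.

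**Conclusion.** The point holds as a conditional one. The primary visit is fixed at exactly the programme's length after baseline, PR starts after baseline by construction, and other sections call that visit post-PR. The two descriptions agree only for participants whose first class falls within about 2–3 days of baseline; for anyone later, the plan as written measures the primary outcome on an unfinished programme. With a 7-day lag, which applies if the monitor week follows the baseline visit, about 2 of 12 sessions are outstanding.

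The cost in power cannot be fixed from the documents. Under the assumptions shown (proportional gain, back-solved SD, two-sided 5%, two-sample test with 57 per arm, the same lag for every PR participant), it is 80% falling to about 65% for a one-week lag and about 46% for two weeks. The timing conflict needs none of these assumptions.

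**What to change.** Reconcile the abstract and the Procedure, Sample size (Stage 2a), Randomisation, Blinding and Physical activity sections, so that the primary assessment has one definition and the position of the monitor week relative to the baseline visit and randomisation is stated.

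Count the primary assessment from randomisation, with a single window applied identically in both arms and set late enough to cover the expected start lag plus the programme as described. Shift the 12-week visit by the same rule. Record each PR participant's start date and the sessions attended by the primary visit, so that the actual overlap can be reported.

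The cost is protocol wording and visit-window settings, with visits in both arms moving by a week or two. The PR programme is unchanged.
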